#### Power Calculations

The sample size for this study is based on detecting a change in PWV as measured by the gold-standard reference device (Complior). We also leverage data from the pilot trial. Previous literature has shown that 4 to 8 weeks of aerobic exercise can reduce PWV by −0.35 (−0.68,−0.02) m/s and a 9‐ to 16-week intervention by −0.69 (−1.13, −0.25) m/s [6]. This outcome is heavily dependent on changes in VO_₂_max; for example, a less than 10% improvement will only result in a −0.4 (−0.52,−0.28) m/s change in PWV, whereas >20% improvement will result in a −1.72 (−2.39,−1.04) m/s change. On the basis of the pilot trial, we estimate that the conservative effect (−0.4 m/s) is more realistic, and this is selected as the expected effect size. We also know from the pilot trial that the SD of PWV is quite large relative to the expected effect size. By sampling the pilot data, we obtain an SD of 1.4 m/s for the 30‐ to 65-year-old age group. Using these numbers in standard power calculations [16] results in a required sample size of 193 per group, assuming 80% power at alpha level of .05 (2-sided test). On the basis of pilot, we also know that the correlation between pre- and postintervention PWV measurements in the control group is high (*R*=0.86) and that the correlation is mostly explained by age, sex, BMI, and blood pressure. While the results will be analyzed using a mixed linear model (see below), for which there is no formal power calculation protocol, we leverage the sample size calculations developed by Borm et al [17] for analysis of covariance and adjust the sample size with (1−⍴^2^), where ⍴ is the correlation coefficient for pre- and postintervention outcome variables. This yields a sample size of 50 per group, and to account for attrition, a 10% increase is considered sufficient, leading to a final sample size of 55 per group. A sensitivity analysis illustrates that with a lower-than-expected pre-post correlation (ρ=0.75), the required sample size increases to approximately 94 participants per group (including 10% attrition). On the other hand, with a higher-than-expected pre-post correlation (ρ=0.95), the required sample size decreases to approximately 21 participants per group.

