To evaluate how strongly candidate mediators account for the intervention-outcome association, each mediator will be entered sequentially into the previously specified linear mixed model, and the resulting change in the intervention regression coefficients will be examined. The proportion of attenuation attributable to each mediator will be calculated as follows: (1−[regression coefficient adjusted for the mediator/regression coefficient adjusted for the determinant])×100%. In parallel, we will assess the incremental predictive value contributed by the intervention effects beyond their presumed mediators. The mediation analyses will be conducted in the full participant population across all randomization groups.

In addition to mediator analyses, we will evaluate prespecified moderators (eg, sex, age, baseline cfPWV, and cardiorespiratory fitness) by extending the primary linear mixed model to include the group×time×moderator interaction. For binary moderators (eg, sex), inference will focus on the group×time×sex term; for continuous moderators, variables will be mean-centered and effects probed at interpretable values (eg, mean, 1 SD) via model-based marginal means and simple-slope contrasts. When an interaction shows evidence of effect modification, we will present stratified (subgroup) estimates and contrasts within moderator levels for interpretation.

These secondary analyses are crucial for exploring potential effects that may be obscured by the ITT analysis, particularly if adherence is low. They will be clearly identified as exploratory and will complement the primary ITT analysis.

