#### Bayesian Analysis Plan

In parallel with the frequentist analysis, we will conduct a Bayesian analysis for the primary and key secondary outcomes (cfPWV and VO_₂_max change). The Bayesian model will mirror the mixed linear model used in the frequentist framework to ensure direct comparability of results; specifically, we will include a random intercept at the individual level, fixed effects for the 3 treatment groups, and covariate adjustment for baseline outcome, age, sex, BMI, and systolic blood pressure. By aligning the model structure, any differences between approaches will reflect the inferential framework (use of priors and posterior probabilities) rather than the model specification.

Priors will be specified transparently and chosen to balance prior knowledge with appropriate uncertainty. For the primary treatment effect on cfPWV, we will use a normal prior with a mean of −0.4 m/s and an SD of 0.5 m/s, centered on our expectation derived from an unpublished pilot study, while allowing the posterior to span both benefit and no effect. For VO_₂_max, we will use a weakly informative normal prior with a mean of 0 and an SD of 5 mL/kg/min, covering plausible changes of −10 to 10 mL/kg/min changes. Covariate effects will receive normal(0, 10) priors to mirror the unpenalized adjustments in the frequentist model. Variance parameters, including the SDs of the individual random intercepts and the residual error, will be given half-Normal(0, 5) priors to provide mild regularization of variability estimates.

The likelihood assumes normally distributed postintervention outcomes with participant-specific random intercepts and a common residual variance. We will sample from the joint posterior distribution of all parameters and assess convergence using split-chain diagnostics (eg, agreement across chains) alongside effective sample size thresholds to ensure stable estimation. Posterior summaries will be presented as means and 95% credible intervals for each treatment contrast (AI vs control; HIIT vs control; and AI vs HIIT), providing directly interpretable intervals for the magnitude and direction of the effects.

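### The group×time×moderator rule does not work when the moderator is the outcome's own baseline, and it does not fit the model set out in the Bayesian plan

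*Protocol article*

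**What the plan says.** The Frequentist Analysis Plan gives one rule for all moderators. It will "evaluate prespecified moderators (eg, sex, age, baseline cfPWV, and cardiorespiratory fitness) by extending the primary linear mixed model to include the group×time×moderator interaction". For continuous moderators, "variables will be mean-centered and effects probed at interpretable values (eg, mean, 1 SD) via model-based marginal means and simple-slope contrasts". Subgroup estimates follow when an interaction shows evidence of effect modification. The section labels these analyses exploratory and applies no significance threshold.

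The same section describes the primary model as a mixed linear model for repeated measures, used to compare mean postintervention cfPWV and VO2max across the three groups. Both outcomes are measured twice, at baseline and after 12 weeks (Abstract, Methods; Study Measurements).

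The Bayesian Analysis Plan says that its model mirrors the frequentist one. It lists a random intercept, fixed group effects, and adjustment for baseline outcome, age, sex, BMI and systolic blood pressure. It lists no time term. Its likelihood is for postintervention outcomes, with "participant-specific random intercepts and a common residual variance".

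The Results section says that no separate statistical analysis plan is currently planned, so this text is the operative specification.

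**The concern.** With two visits, a time factor exists in the model only if the baseline measurement is itself an outcome row. When the moderator is the same outcome's baseline, that row and the moderator are the same number. The model then predicts the baseline row from itself without error, and that false precision enters the common residual variance.

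One planned quantity is at stake: the AI-versus-control marginal mean at week 12, at given levels of baseline stiffness. It is a natural one to report, because the primary model is described as comparing postintervention means. The article intends to interpret effect sizes and their uncertainty rather than thresholds, so an interval that is too narrow does harm even where no P value is dichotomised.

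A second, separate matter is within-arm change. At high or low baseline it contains regression to the mean, and marginal means shown per arm would display it.

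**Working it through.** **Inputs (Power Calculations).** SD: "we obtain an SD of 1.4 m/s for the" 30-to-65 age group. Correlation 0.86: "correlation between pre- and postintervention PWV measurements in the control group is high". Effect: "we estimate that the conservative effect (−0.4 m/s) is more realistic". Error rates: "assuming 80% power at alpha level of .05 (2-sided test". Size: "leading to a final sample size of 55 per group". The article states no error rate for the moderator analysis.

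**The plan's own figure.** The two-sample formula with difference 0.4 and SD 1.4 gives 193 per group. Then 193 × (1 − 0.86²) = 193 × 0.2604 = 50.3, taken as 50, and 50 × 1.10 = 55. The sample size reproduces, so SD 1.4 and correlation 0.86 can be carried forward.

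**Residual variance with time in the model.** The true week-12 variance given baseline is 1.4² × (1 − 0.86²) = 1.96 × 0.2604 = 0.510. The full group×time×baseline expansion has 12 coefficients. Every baseline residual is zero, so the residual sum of squares comes from week 12 alone but is divided by 2N − 12 instead of N − 6. With N = 165 that is 318 instead of 159. The estimate is exactly half: 0.255. As one residual of each pair is zero, there is no within-person residual correlation, and the random-intercept variance goes to zero. A direct mixed-model fit to one simulated trial gave residual variance 0.251 against 0.502, with an intercept variance of about 0.

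**Week-12 contrast, AI versus control, at the mean, 55 per group.**
- Correct SE: √(2 × 0.510 / 55) = 0.136 m/s.
- SE from the model: √(2 × 0.255 / 55) = 0.096 m/s, too small by √2.
- False-positive rate: 2 × [1 − Φ(1.96/√2)] = 16.6%. Coverage of a nominal 95% interval: 100% − 16.6% = 83.4%.

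**Contrast of change.** The model adds the halved variance once for each visit: 0.255 + 0.255 = 0.510. The two errors cancel and the SE is right. The three-way term is also a contrast of change, so it holds its level too.

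**Simulation with no true effect** (55 per group, SD 1.4, correlation 0.86, 6,000 trials):

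| Quantity | False positives |
|---|---|
| Week-12 contrast at +1 SD / mean / −1 SD | 16.9% / 16.6% / 16.7% |
| Between-group change contrast at +1 SD | 5.4% |
| group×time×baseline term | 5.4% |
| Week-12 model with group×baseline: contrast at +1 SD | 5.2% |
| Week-12 model with group×baseline: interaction | 5.3% |

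With four covariates added, the week-12 contrasts gave 15.4% to 15.8%. With 50 per group, or correlation 0.75 or 0.95, they gave about 17% to 18%. A general-purpose mixed-model routine returned no usable fit in 269 of 300 simulated trials, because the solution lies on the boundary. An analyst may therefore meet a failed fit instead of a narrow interval.

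**With week-12 values only.** There is one outcome per person and no time factor. The group×time×moderator term does not exist, and the random intercept cannot be separated from the residual.

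**Within-arm change.** With no effect and equal SDs at both visits, expected change at +1 SD of baseline is −(1 − 0.86) × 1.4 = −0.196 m/s, and at −1 SD it is +0.196 m/s. The simulation gave −0.197 and +0.196. At +1 SD the figure runs from −0.07 (correlation 0.95) to −0.35 m/s (correlation 0.75). The shift is the same in every arm: the mean AI-versus-control difference in change at +1 SD was −0.002 m/s.

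**The case against.** The strongest reply is that the failing model is put together from two sections that disagree. The time factor comes from the Frequentist Analysis Plan. The common residual variance comes from the Bayesian Analysis Plan, where the same sentence restricts the likelihood to postintervention outcomes. On that second reading the moderator term reduces naturally to group×baseline at week 12, which holds about 5%. This stands in part: the repeated-measures form is inferred from the time term and the repeated-measures description, and on the other reading no interval is wrong. But the written term then cannot be fitted, so the text needs changing either way.

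A reader might infer that all the planned probing has a 17% false-positive rate. The documents do not support that. They do not say whether week-12 means or changes will be contrasted, and contrasts of change and the three-way test hold their level. Subgroup estimates are also presented only after that three-way test shows evidence.

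A reader might also infer that regression to the mean would appear as a benefit of AI coaching that reaches the −0.2 m/s mark. It would not. The shift is equal in all randomised arms, cancels in AI versus control, and shows as worsening at −1 SD. The −0.2 m/s example in the Bayesian Analysis Plan is defined for the AI-versus-control effect, so a within-arm figure cannot be set against it. No section expressly plans to interpret within-arm change by baseline level.

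Finally, the analyses are exploratory and use no threshold. That limits the importance but does not repair the interval.

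**Conclusion.** The point holds in a limited form. The stated rule is either degenerate (time kept) or unfittable (week-12 values only) when an outcome is moderated by its own baseline: cfPWV by baseline cfPWV, and VO2max by baseline fitness. In the first case the damage is confined to between-group week-12 marginal means, with standard errors too small by √2, about 17% false positives and about 83% coverage. This assumes two visits, a random intercept and one common residual variance. The factor does not depend on the SD or the correlation.

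Within-arm change at ±1 SD of baseline carries about ∓0.2 m/s of regression to the mean at correlation 0.86. It must not be read as benefit, but it does not bias the comparison between groups.

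Sex and age as moderators, and baseline cfPWV as a moderator of VO2max, do not share this fault. The primary AI-versus-control result is not touched. Severity is low.

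**What to change.** Reconcile the Frequentist and Bayesian Analysis Plans on whether baseline is an outcome row or a covariate. Then add one sentence to the moderator paragraph: where the moderator is the outcome's own baseline, the week-12 value is regressed on group, baseline, group×baseline and the listed covariates (age, sex, BMI, systolic blood pressure), and only between-group contrasts at the mean and ±1 SD of baseline are reported, not within-arm change by baseline level.

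The current rule can stay for sex, age and other moderators. If the sponsor settles on week-12 values only, the time factor drops out of those terms as well.

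The cost is one sentence and one alternative model call, with no new data or participants. Nothing is lost for people without a week-12 value, since an exactly fitted baseline row carries no information on the contrast. The Randomization section keeps analysts blinded to group codes until the intention-to-treat analysis is complete, so the change can be made before codes are known. If the sponsor regards it as a significant amendment, the article's route is notice to the ethics committee and the registry.

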#### Frequentist Analysis Plan

The primary frequentist analysis will be based on the ITT framework, defined as all randomized participants included in the groups to which they were initially assigned, regardless of adherence or withdrawal. The mixed linear model (see below), which inherently accommodates longitudinal data with missing time points under the assumption of missing at random, will be the primary method used to analyze this ITT population. The ITT analysis provides an unbiased estimate of the intervention’s effectiveness under real-world conditions. However, we expect highly motivated participants to engage the most in their assigned interventions and thus receive the most benefit. This will be investigated in mediator analyses. The intervention may work differently for certain people (eg, men vs women), and these will be studied as moderators. Both mediator and moderator analyses are described below.

The difference between the AI group and the Oura Ring only group will be considered the primary comparison, while differences across other group pairs will be exploratory. The primary analysis will be based on a mixed linear model, which is an appropriate method for analyzing repeated measures data while accounting for individual-level variability. This model will be used to assess the effectiveness of the interventions and compare the mean postintervention cfPWV and VO_2_max across the 3 study groups. We will assume that any missing data are missing at rMissing At Random. The results will be presented with full, numeric *P* values, mean differences, and 95% CIs, avoiding an arbitrary (eg, *P*=.05) dichotomy into statistically “significant” and “insignificant.” No formal correction for multiple comparisons will be applied. Instead, we used a linear mixed model, which induces partial pooling of group-level estimates. As discussed by Gelman et al [18], this approach reduces the risk of overestimating spurious differences that can arise from multiple comparisons, thereby mitigating concerns related to multiple testing. Accordingly, we will focus on effect sizes and their uncertainty rather than dichotomous significance testing.

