##### Quantitative Descriptive Process Evaluation

Questionnaire data will be summarized descriptively to provide additional context for interpreting study outcomes. RM4-FM and ESES scores will be reported as means and SDs (or medians and IQRs if nonnormally distributed) at baseline and 12 weeks for each group. Within-group descriptive changes over time will be summarized. Engagement metrics, including Oura App analytics and frequency and length of Advisor chat interactions, will be reported descriptively. Advisor chat analytics will be generated using Nebuly, a user analytics platform for LLM applications that automatically captures conversational interactions while anonymizing personal information; these data will provide aggregate summaries, such as the number and length of conversations, common user intents, and interaction drop-off points. These data are not intended for mediation or moderation analyses but to contextualize participants’ reported experiences of the study and interventions.

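### Percent attenuation of the group coefficient is assigned to the adherence question, but it splits the ITT effect and does not estimate the effect of adhering

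*Protocol article*

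**What the plan says.** Under Frequentist Analysis Plan, the protocol article makes ITT primary. It then expects highly motivated participants to engage most and so benefit most, and adds: "This will be investigated in mediator analyses." The method follows in the same section: "each mediator will be entered sequentially into the previously specified linear mixed model", with the result expressed as one minus the ratio of the adjusted to the unadjusted intervention coefficient, times 100%, across all randomized groups. After a paragraph on moderators, whose named examples are all baseline characteristics, the section closes: "These secondary analyses are crucial for exploring potential effects that may be obscured by the ITT analysis, particularly if adherence is low." It labels these analyses exploratory.

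Two other places bear on the point. Process Evaluation takes HIIT attendance, and in the AI arm the number and frequency of Advisor interactions, as the measures of delivery. Quantitative Descriptive Process Evaluation covers the questionnaires, app analytics and Advisor chat metrics, and says: "These data are not intended for mediation or moderation analyses." The statistical sections describe no complier-average, instrumental-variable, per-protocol or dose-response analysis, and the Results section says no separate SAP is currently planned.

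**The concern.** The question asked is what the intervention does for people who take it up. The tool assigned to it answers another question: how much of the ITT effect runs through a given variable. When the effect works through engagement, adjusting for engagement moves the group coefficient towards zero. So if adherence is low, the reported quantity is a fraction of an already diluted effect, not the effect that dilution hid.

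The protocol also names the likely confounder. Motivation drives engagement, and it may affect cfPWV by other routes. Engagement is not randomized, so both the adjusted group coefficient and the mediator's own coefficient can then be biased.

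The summary measure is a ratio with the ITT coefficient as denominator, so it is least stable when that coefficient is small, which is when the plan most wants to use it. A reader could be shown a large attenuation percentage, or a group coefficient of the wrong sign, as evidence about adherence.

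**Working it through.** **Inputs from Power Calculations.** Effect: "we estimate that the conservative effect (−0.4 m/s) is more realistic, and this is selected as the expected effect size". SD: "we obtain an SD of 1.4 m/s for the 30‐ to 65-year-old age group". Unadjusted size: "required sample size of 193 per group, assuming 80% power at alpha level of .05 (2-sided test". Pre-post correlation: "measurements in the control group is high (*R*=0.86".

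**The plan's own figures reproduce.**
- 2 × (1.960 + 0.842)² × 1.4² / 0.4² = 192.3, rounded up to 193.
- 193 × (1 − 0.86²) = 193 × 0.2604 = 50.3, stated as 50; 50 × 1.10 = 55.
- Residual SD after baseline adjustment = 1.4 × √0.2604 = 0.714. SE of a two-arm difference at 50 per arm = 0.714 × √(2/50) = 0.143.

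**Dilution of ITT.** The documents give no adherence rate, so a range is assumed. If the effect is -0.4 m/s in adherers and zero otherwise:

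| Adherence | ITT effect (m/s) | Power at 50 per arm |
|---|---|---|
| 100% | -0.40 | 80% |
| 75% | -0.30 | 56% |
| 50% | -0.20 | 29% |
| 25% | -0.10 | 10% |

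The plan is therefore right that low adherence can obscure an effect.

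**What mediator adjustment does.** Take 50% adherence, all-or-none, possible only in the AI arm, with the whole effect running through it. In the adjusted model the group coefficient compares AI-arm non-adherers with controls, and the adherence coefficient compares adherers with non-adherers within the AI arm.
- No confounding: group coefficient 0.00, attenuation 1 − 0/(−0.20) = 100%, adherence coefficient -0.40.
- Confounding: assume the more motivated half adheres and motivation changes cfPWV by -0.2 m/s per SD. The mean of a standard normal above its median is 0.798. The group coefficient is −0.2 × (−0.798) = +0.16. Attenuation is 1 − 0.16/(−0.20) = 180%. The adherence coefficient is −0.4 − 0.2 × (2 × 0.798) = -0.72, against a true -0.40.
- ITT divided by the adherence share, −0.20/0.50, gives -0.40 in both cases. Large-sample simulation agrees with all of these values.

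A second simulation used graded engagement that also varies in controls. At 50% adherence the group coefficient went from -0.20 to 0.00 (fully mediated) or -0.10 (half mediated). With the same -0.2 m/s per SD of motivation and full mediation it went to about +0.39. The size depends on the setup, but in no scenario did adjustment bring the group coefficient to -0.40.

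**Stability of the percentage.** With 50 per arm, no confounding and an assumed true mediated share of 50%:
- total effect -0.2 m/s: 95% range about -350% to 490%;
- total effect -0.4 m/s (the plan's value): roughly 0% to 180%.

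These are tail percentiles of a ratio and shift with the mediator's distribution and between runs; a repeat with the all-or-none mediator gave -325% to 519% and 0% to 190%.

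**What the randomization-based estimate adds.** At 50 per arm and ITT -0.2 m/s, P<.05 occurred in 28% of simulated trials for ITT and 29% for the instrumental estimate, whose 95% sampling range was about -0.98 to +0.19 m/s.

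**The case against.** The strongest reply is that a smaller group coefficient is what mediation is meant to produce. The section's stated aim is to see how far mediators account for the association, and in the fully mediated, unconfounded case a coefficient of zero is the correct answer. The mediator's own coefficient in that model recovers about -0.40. All of this stands, but only without confounding, and the plan reports the change in the group coefficient, not the mediator's coefficient.

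Several stronger readings are tempting and should not be made:
- A reader might infer that no engagement variable is left for mediation. The exclusion covers questionnaire, app and Advisor-chat data. It does not reach HIIT attendance, or the Oura-measured leisure-time activity collected in all three groups (Interventions, Overview).
- A reader might take sequential entry as cumulative, so that each share depends on order. It can equally mean one mediator after another, singly, and the formula's single mediator fits that.
- The closing sentence covers moderators too, so it is not a claim about mediators alone. The named moderators are baseline traits, though, and do not measure adherence.
- The widest attenuation range belongs to a halved effect. At the plan's -0.4 m/s it is much narrower, though still uninformative.
- A complier-average estimate would not detect what ITT misses. It rescales ITT and adds no power.

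The analyses are labelled exploratory, which limits the harm but does not make the method answer the question.

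**Conclusion.** The concern holds in limited form. Percent attenuation does not estimate the effect of adhering, so it cannot carry the role given to it when adherence is low. Under the confounding that the plan's own remark on motivation makes plausible, the adjusted group coefficient can change sign (+0.16 against an ITT of -0.20) and the mediator coefficient can be well off (-0.72 against -0.40). These sizes rest on assumed values: 50% adherence, the more motivated half adhering, and -0.2 m/s per SD of motivation. The attenuation ranges rest on an assumed 50% mediated share and the plan's SD and correlation.

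Separately, the passage sending engagement to mediation and the passage barring app and Advisor-chat data from it need reconciling, because Advisor interactions are the delivery measure for the AI arm, which is in the primary comparison. The primary ITT analysis is unaffected.

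**What to change.** 1. For the adherence question, add an exploratory randomization-based estimate (instrumental-variable or complier-average) for AI versus control, with Oura-measured activity as the exposure. State the exclusion restriction, namely that the coach affects the outcome only through the measured activity. State also that the estimate rescales the ITT effect, has wide intervals, adds no power, and becomes unstable if the coach barely changes activity.
2. Keep mediation for mechanism only. Say explicitly that mediators enter one at a time. In place of a bare percentage, report the indirect effect with a bootstrap interval, adjusted for the baseline mediator and baseline outcome, and acknowledge possible confounding by motivation.
3. Reword the closing sentence so that it no longer presents mediator adjustment as a way to uncover effects hidden by low adherence.
4. Name the engagement variables to be used as mediators and make this agree with Quantitative Descriptive Process Evaluation, either by confirming that app and chat data stay descriptive or by lifting that exclusion.

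The cost is wording and a small extra analysis on data already collected in all groups. Neither the sample size nor the primary analysis changes.
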